### Study Outcomes

#### Primary Outcome: Physical Activity

The primary outcome will be weekly MVPA minutes assessed via hip-worn accelerometers (ActiGraph wGT3X-BT). Participants will wear the accelerometers for 1-week periods throughout the 6-week intervention. Participants will be asked to wear the device every day during waking hours, removing it only for sleep or when engaging in activities involving water (eg, showering, swimming). Data from accelerometers are well-validated [64,65]. We will use self-reported MVPA minutes using the 7-day PAR as a secondary measure of physical activity.

#### Mechanisms

##### Affective Evaluations

We will use measures of affective response to exercise and intrinsic motivation for exercise to assess affective evaluations. The Feeling Scale (FS) [66] measures affective response to exercise and will be assessed during and postexercise for the in-person walking sessions each week. The FS is a single-item measure of core affect, in which participants rate their current feelings on an 11-point scale ranging from −5 (very bad) to 5 (very good). The intrinsic subscale of the Behavioral Regulations in Exercise Questionnaire (BREQ-2) [67] will be administered after listening to the audio recording in person. Intrinsic motivation is assessed with 4 items (eg, “I exercise because it’s fun”) on a 5-point response scale ranging from 0 (not true for me) to 4 (very true for me).

##### Temporal Discounting

We will use a computerized delayed discounting task [68] to assess preference for immediate versus future rewards. This task will involve participants indicating their preference for smaller quantities of money that are available immediately versus larger amounts of money available sometime in the future.

##### Action Planning

A 4-item measure of action planning [30] will be administered after participants listen to the audio recording in person each week. Items (eg, “I have made a detailed plan regarding when to exercise”) are rated on a 4-point response scale ranging from 0 (completely disagree) to 3 (completely agree).

Figure 2 shows the assessment schedule of the key study variables.

**Figure 2 figure2:**
[figure not shown]
Timing of assessments, intervention delivery, and physical activity within each in-person session. PA: physical activity; PAR: Physical Activity Recall.

### Intervention Adherence

All participants will listen to their assigned intervention recording during the in-person visits. For participants in the high dose condition, we will assess adherence via 2 sources: self-reports and tracking data that indicates access and time spent on the audio recording. For self-reported adherence, high dose participants will be asked at the beginning of each in-person visit to indicate how many days during the past week they listened to the audio recording.

### Optimization Decisions

Following recommendations for optimization [15], we will start by examining main effects of the 4 intervention components, provisionally include components that have a significant effect on physical activity, and provisionally exclude components that do not. Next, we will examine interactions, starting with the 2-way interactions, to determine whether any decisions about provisional inclusion and exclusion should change. We will then use participant burden and acceptability to evaluate remaining potential combinations. A combination of components that results in less time for participants will be considered preferable to a longer intervention that produces the same effect on physical activity. Only guided thinking components rated as acceptable will be included in the final intervention package.

### Statistical Analyses

#### Preliminary Analyses and Missing Data

Univariate and multivariate outliers will be identified and corrected following the data screening guidelines of Tabachnick and Fidell [69]. Patterns of missing data will be examined [70]. Multilevel modeling (MLM), which uses maximum likelihood procedures to handle missing data, will be used to address the research questions [71].

#### Analysis Plan

The first aim is to identify the optimal combination of components for meeting weekly physical activity minute guidelines. MLMs will be used to account for the nested structure of the data (ie, 6 weekly assessments nested within participants). Weekly physical activity minutes will be the dependent variable; time (weeks 0-5) will be a within-person predictor, and the main effects for each intervention component, along with all 2-way and higher order interactions, will be included as between-person predictors.

The second aim is to determine the mechanisms of each intervention component. A series of MLMs, similar to models of the first aim, will test the extent to which (A) each intervention component is associated with within-person change in its putative mechanism, and (B) the within-person change in each mechanism is prospectively associated with physical activity minutes.

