### Screening

Initial eligibility will be determined with an online prescreen questionnaire, in which potential participants will report their physical activity for a typical week over the past 6 months using items from the International Physical Activity Questionnaire (IPAQ) [61]. They will also report on the inclusion criteria and exclusionary health conditions. Eligible participants will be contacted to schedule a telephone screen and a baseline study visit and to complete an initial COVID-19 screen in which they will be asked to self-report COVID-19 symptoms and their vaccination status.

On the day prior to the baseline study visit, we will assess participants’ physical activity during the past week using the telephone-based 7-day Physical Activity Recall (PAR), a valid and reliable measure of physical activity [62]. Participants who report >150 minutes of MVPA on this assessment will be excluded from participation. We will conduct this assessment on the day prior to the baseline visit to avoid turning away ineligible participants after they have already shown up in person. This assessment will serve as the baseline measure of participants’ physical activity.

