### Randomization

We will stratify randomization based on 2 levels of baseline MVPA to explore the extent to which baseline MVPA moderates intervention effects: (1) individuals who report <60 minutes of weekly MVPA (ie, inactive or underactive) and (2) those who report between 60 and 149 minutes of weekly MVPA (ie, insufficiently active). These MVPA cutoffs reflect meaningful distinctions in current physical activity recommendations [1]. We will aim to recruit and enroll an equal number of individuals from both groups. Within each MVPA group, we will use block randomization with block sizes of 16 (ie, the total number of experimental conditions). We will use a random number generator to determine the random sequence within each block. The principal investigator will generate the random allocation sequence for each stratified randomization grouping. An RA will enroll and assign participants to their study condition.

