### Sample Size and Power

Based on a small-to-moderate effect size (Cohen *d*=0.40) [72] and assuming a correlation of at least *r*=.40 between pre- and postintervention physical activity levels, a sample size of 176 will be sufficient to detect significant effects with 80% power and a Type I error rate of .05. This sample size estimate was generated using the Factorial Power Plan macro in SAS software, which is specifically designed to calculate power for factorial designs [73]. The sample size (N=176) will provide a sufficient number of participants while also maintaining balanced cell sizes (n) across the 16 experimental conditions, an important design feature for maintaining power for tests of the main effects and interactions [15,74]. We will enroll a total of 192 participants to account for attrition (~10%) and to maintain balanced numbers across the conditions. The factorial design is sufficiently powered for all tests, including the interactions, because the tests involve comparisons of means computed across aggregates of experimental conditions [15,73].

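### The Aim 1 model lists neither baseline MVPA nor the randomisation stratum, although the stratification and the sample size both rely on baseline: a precision loss that is cheap to repair

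*Protocol article*

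**What the plan says.** Four sections of the protocol article bear on this point.

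- **Analysis Plan.** The outcome is weekly activity minutes, with six weekly assessments nested within participants. Time (weeks 0-5) is the within-person predictor. For the rest, "the main effects for each intervention component, along with all 2-way and higher order interactions, will be included as between-person predictors". No baseline measure and no stratum is listed.
- **Screening.** A telephone 7-day PAR is taken the day before the baseline visit: "This assessment will serve as the baseline measure of" physical activity.
- **Randomization.** "We will stratify randomization based on 2 levels of baseline MVPA to explore the extent to which baseline MVPA moderates intervention effects". The levels are below 60 and 60 to 149 minutes per week.
- **Sample Size and Power.** The calculation is "Based on a small-to-moderate effect size (Cohen *d*=0.40" and "assuming a correlation of at least *r*=.40 between pre- and postintervention physical activity levels". It concludes that "a sample size of 176 will be sufficient to detect significant effects with 80% power and a Type I error rate of .05", with the further aim of "maintaining balanced cell sizes (n) across the 16 experimental conditions".

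**The concern.** Baseline activity is collected, used to stratify and credited in the sample size, but it does not appear in the model that is to be fitted. Nor does it enter as an extra wave of the outcome. Under Baseline Visit, participants hear the recording and are then shown how to wear the accelerometer, so all six accelerometer weeks follow the first exposure. The PAR is the only pre-exposure measure of activity.

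A pre-post correlation improves precision only when the analysis uses the pre value. If randomisation is balanced on a prognostic factor and the factor is then left out, variance that it explains stays in the error term and the standard errors are larger than they need be. This bears on the trial's decisions: under Optimization Decisions, components with a significant effect are provisionally kept and the others provisionally dropped. Lost precision therefore raises the chance of dropping a component that works.

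**Working it through.** **Inputs from Sample Size and Power and Study Design:** d = 0.40; pre-post r = .40; alpha .05; power 80%; 16 equal cells; 1:1 allocation per component (88 v 88 at N = 176). The article does not state sidedness, so two-sided is assumed.

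**Step 1. Reproduce 176.** For a main effect on one post value, use a noncentral t with

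ncp = d × √N / (2 × √v), df = N − 16, less 1 for a covariate,

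where v is the residual variance relative to the outcome variance: v = 1 without baseline, and v = 1 − r² = 1 − .16 = .84 with it.

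| Analysis of one post value | v | ncp at 176 | Power at 176 | N for 80% | Next multiple of 16 |
|---|---|---|---|---|---|
| Baseline covariate, r = .40 | .84 | 2.895 | 82.1% | 167 | **176** |
| Baseline covariate, r = .20 | .96 | 2.708 | 76.8% | 191 | 192 |
| No baseline | 1.00 | 2.653 | 75.1% | 199 | 208 |
| Change score, 2(1 − r) | 1.20 | 2.422 | 67.3% | 238 | 240 |

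For example, without baseline ncp = 0.40 × √176 / 2 = 2.653; with baseline it is 2.653 / √.84 = 2.895.

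Other variants, by normal approximation and rounded up to a multiple of 16, also miss 176:

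- one-sided without baseline: 160
- one-sided with baseline: 144
- one-sided change score: 192
- variance factor (1 − r): 128 two-sided, 96 one-sided

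Among the variants tried on the stated inputs, only two-sided baseline adjustment gives 176.

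**Step 2. Allow for six weekly measures.** The Aim 1 model does not rest on one post value. Let ρ be the correlation between any two weeks, and let baseline correlate r with each week. Relative to the variance of one week, the six-week mean has variance (1 + 5ρ)/6, or (1 + 5ρ)/6 − r² after adjustment. The article gives no ρ, so .4 to .9 is an assumed range. Power at N = 176, by normal approximation:

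| ρ (assumed) | (1 + 5ρ)/6 | No baseline | Adjusted, r = .20 | Adjusted, r = .40 |
|---|---|---|---|---|
| .4 | .500 | 96.3% | 97.5% | 99.5% |
| .6 | .667 | 90.1% | 91.8% | 96.1% |
| .8 | .833 | 82.8% | 84.6% | 89.9% |
| .9 | .917 | 79.1% | 80.9% | 86.2% |

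Unadjusted power falls below 80% only when ρ exceeds about .87. Adjustment helps in every row: by about 3 to 7 points at r = .40, and by 1 to 2 points at r = .20.

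**The case against.** - **The article is condensed.** It says that these terms will be included, not that no others will be. It gives no covariance structure, and covariate lists are often left to a fuller plan. If the sponsor powered a baseline-adjusted analysis, a baseline covariate may well have been intended. This softens the point but does not remove it: the list runs down to higher-order interactions, and as written it does not fit two other sections of the same article.
- **The reproduction is not unique.** The unrounded figure is 167, and 176 appears only after rounding to equal cells; the article does state that aim. A six-week mean without baseline and ρ near .8 needs 164, which also rounds to 176, but that uses an input the article does not give.
- **A baseline covariate would not fully align the two sections.** The sample size reads as a pre-post calculation and the model has six waves. That is so, but the covariate would at least use the correlation that was credited.
- **The gain may be small.** Baseline is self-reported and restricted by eligibility, while the outcome is measured by accelerometer. A correlation of .40 across the two instruments is the sponsor's assumption. At .20 the gain is 1 to 2 points.
- **A reader might infer that the planned moderation analysis is missing.** The documents do not support that. Randomization describes moderation by baseline MVPA as something to explore, and an exploratory moderator need not be in the primary model.

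**Conclusion.** The point holds as a matter of precision and consistency. As listed, the Aim 1 model leaves out a baseline measure that the trial collects, stratifies on and credits in its sample size. On the article's own single-post-measure basis, this is the difference between 82% and 75% power at N = 176. For the six-week mean, over assumed between-week correlations of .4 to .9, it is about 99% to 86% against 96% to 79% when r = .40.

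Two stronger readings are tempting. A reader might take 75% as the power of the trial. The documents do not support this, because the planned model uses six weekly measures and unadjusted power stays above 80% unless the between-week correlation is above about .87. A reader might also infer biased component effects. Under 1:1 stratified randomisation, omitting the stratum leaves the estimates unbiased and makes the tests, if anything, conservative.

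The result rests on a two-sided test, the article's d and r, equal cells, and an assumed common between-week correlation. It is a low-cost improvement, not a flaw that must be corrected for the trial to be valid.

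**What to change.** Add one sentence to the Analysis Plan, before analysis begins, pre-specifying continuous baseline PAR MVPA and the two-level randomisation stratum as between-person covariates in the Aim 1 model. Moderation by baseline MVPA can stay in a separate exploratory model with stratum-by-component terms. If these covariates were always intended, stating so is enough.

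The cost is two degrees of freedom and two terms in the analysis code, with no new data. Timing matters: the article's Results section reports 41 participants enrolled as of July 2022 and says that analysis will follow completion of data collection. Covariates fixed before the outcomes are examined cannot be read as chosen for their effect on the result.

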### Sample Size and Power

Based on a small-to-moderate effect size (Cohen *d*=0.40) [72] and assuming a correlation of at least *r*=.40 between pre- and postintervention physical activity levels, a sample size of 176 will be sufficient to detect significant effects with 80% power and a Type I error rate of .05. This sample size estimate was generated using the Factorial Power Plan macro in SAS software, which is specifically designed to calculate power for factorial designs [73]. The sample size (N=176) will provide a sufficient number of participants while also maintaining balanced cell sizes (n) across the 16 experimental conditions, an important design feature for maintaining power for tests of the main effects and interactions [15,74]. We will enroll a total of 192 participants to account for attrition (~10%) and to maintain balanced numbers across the conditions. The factorial design is sufficiently powered for all tests, including the interactions, because the tests involve comparisons of means computed across aggregates of experimental conditions [15,73].

## Results

This project was funded by the National Cancer Institute (R21CA260360) on May 13, 2021, with a start date of May 15, 2021, and an end date of April 30, 2023. Recruitment and data collection began in February 2022, and 41 participants have enrolled in the study as of July 2022. Data collection is expected to be completed in summer 2023. Data analysis will begin after the completion of data collection.

## Discussion

### Study Implications

Delivering interventions to promote physical activity via technology-based platforms (eg, smartphone apps, websites, audio recordings) is a promising avenue to address scalability and dissemination barriers among existing interventions. The GeT Active optimization study is innovative because it identifies optimal combinations of intervention components and unpacks the “black box” in early-phase development (vs later on in the process), consistent with current frameworks of intervention development [15,20,21].

The results expected from the GeT Active optimization study will inform future refinements, testing, and use of these guided thinking tasks to promote physical activity. For example, if multiple combinations are equally effective for physical activity, this could result in a package of components that is flexible and customizable for future use (ie, individuals choose which components they want to use). Evidence on the effect of frequency of use (ie, dose) will be important in refining the intervention and subsequent dissemination, particularly if 1 component benefits from multiple uses but the others do not. We also anticipate a diverse sample with different baseline physical activity levels that will allow us to explore individual differences in the effect of the intervention components (eg, by race/ethnicity and physical activity levels).

The results from the GeT Active optimization study will also accelerate the development of the intervention more efficiently than standard approaches, which tend to either test multiple intervention components as an entire package or disparately in stand-alone studies [15]. By testing combinations of the guided thinking tasks and their frequency of use in a factorial study, we will know how the components work synergistically (or antagonistically) with each other rather than just their independent effects, as previous studies have done [17,23,26,35,41]. Moreover, by testing putative mechanisms of the components, we will be positioned to understand why components are (or are not) effective, which will help us identify which components need refinement, further optimization, or reconsideration [59].

### Limitations

The study has a few limitations. First, the intervention lasts for 6 weeks, which is a short period of time to observe effects on physical activity. We sought to balance the need to enroll a sufficient number of participants to provide a rigorous test of the guided thinking components and their combinations with a follow-up period long enough to observe sufficient variability in physical activity adherence. We are confident that 6 weeks will be long enough to provide meaningful tests of the components on physical activity, as prior studies have observed that participants begin to show meaningful variability in physical activity adherence within 4 to 6 weeks [75-77]. A longer intervention period is better suited for an efficacy trial in the final phase of intervention optimization (ie, evaluation) [15]. Second, participants in the high dose conditions receive reminders to listen to their audio recording 4 times per week via text message. These reminders could serve as an additional intervention component. Therefore, we opted to contact all participants 4 times per week via text message to increase study engagement for all participants and to ensure any potential effect of the reminders is constant across conditions. Third, the intervention dose amounts are at 2 extremes, once a week and 5 times per week. This will limit our ability to determine optimal intervention dosage. We will be able to clearly determine whether listening to the audio recording once a week is as effective as multiple times per week. If results indicate that listening multiple times per week is more effective, this will signal the importance of further specifying optimal doses in follow-up investigations.

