### Objective of the GeT (Guided Thinking) Active Study

The overall objective of the GeT Active study is to optimize a scalable guided thinking intervention to promote physical activity, using principles of the MOST framework [15]. We will evaluate effects of the components on physical activity over 6 weeks in a 2 (EFT vs recent thinking) × 2 (PAI vs neutral imagery) × 2 (planning vs no planning) × 2 (dose: high vs low) full factorial randomized trial. We will use the following criteria to evaluate findings and identify the optimal combination of intervention components: effect of components on physical activity, efficiency (ie, identify inert components, antagonistic effects), participant burden (ie, total recording length, intervention dose), and acceptability of each guided thinking component. Mechanism-focused analyses will inform which components are optimal candidates for inclusion and which need refinement or reconsideration [59].

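### A non-significant dose effect would not show that once-weekly listening is as effective as more frequent listening, yet the protocol says the trial will settle this clearly.

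*Protocol article*

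**What the plan says.** In the Limitations section, after conceding that two extreme doses restrict what can be learned about the best dose, the article says: "We will be able to clearly determine whether listening to the audio recording once a week is as effective as multiple times per week".

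Dose is the fourth of the four components (Intervention Component Evaluation), so the rule in Optimization Decisions applies to it: "provisionally include components that have a significant effect on physical activity, and provisionally exclude components that do not". Interactions are then examined, and may change those provisional decisions. Burden and acceptability come last: "A combination of components that results in less time for participants will be considered preferable to a longer intervention that produces the same effect". The study objective also lists, among its criteria, "efficiency (ie, identify inert components, antagonistic effects").

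Sample Size and Power gives the only sizing. For a standardised difference of 0.40, and "assuming a correlation of at least *r*=.40 between pre- and postintervention physical activity levels", it says "a sample size of 176 will be sufficient to detect significant effects with 80% power and a Type I error rate of .05".

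The article gives no margin and no confidence-interval rule. It does not define what counts as equally effective, as having the same effect, or as inert.

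**The concern.** Saying that once weekly is as effective as five times weekly is a claim of equivalence, or at least of non-inferiority. The design described is a superiority design: it is sized to find a difference, and the criterion is whether a difference is significant. When such a test is not significant, either there is no difference of importance or the estimate is too imprecise to tell. The test alone does not separate the two.

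The dose decision is at stake. If more frequent listening has a real but modest benefit, a null test is a likely result. The sentence in Limitations would then invite the reader to take that null as a clear finding that once a week suffices. The same difficulty arises when two packages are judged to have the same effect and the shorter is preferred.

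**Working it through.** **Inputs.** From Sample Size and Power: d = 0.40, r = .40, N = 176, 80% power, Type I error .05 (sidedness not stated; two-sided assumed), and a design sized "while also maintaining balanced cell sizes (n) across the 16 experimental conditions". That gives 176/16 = 11 per condition and 88 per dose level. From Analysis Plan: six weekly values per participant. SD units are those of a single weekly measure.

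**The plan's own figure.** With the pre-intervention value as covariate, the residual SD is √(1 − 0.40²) = 0.917. Then n per level = 2 × (1.960 + 0.842)² × 0.84 / 0.16 = 82.4, so 83 per level and 166 in total. The next multiple of 16 is 176. Power at 88 per level is 82.5%. The stated sample size is reproduced, as a superiority calculation.

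**Precision of the dose effect.** SE = SD × √(2/88). For a six-week average with equal within-person correlation ρ and no baseline covariate, SD² = (1 + 5ρ)/6: 0.50 at ρ = 0.4 and 0.833 at ρ = 0.8. The article gives no ρ, so this range is an assumption.

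- 95% half-width = 1.96 × SE.
- P(not significant | true d) = Φ(1.96 − d/SE) − Φ(−1.96 − d/SE).
- Equivalence power at true difference 0, 90% interval inside ±m: 2Φ(m/SE − 1.645) − 1, set to zero if negative.

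| Outcome | SE | 95% half-width | Not significant, d = 0.20 | Not significant, d = 0.30 | Equivalence power, ±0.40 | Equivalence power, ±0.20 |
|---|---|---|---|---|---|---|
| Single measure, r = .40 | 0.138 | 0.27 | 70% | 42% | 79% | 0% |
| Single measure, no baseline | 0.151 | 0.30 | 74% | 49% | 69% | 0% |
| Six-week mean, ρ = 0.4 | 0.107 | 0.21 | 53% | 20% | 96% | 18% |
| Six-week mean, ρ = 0.8 | 0.138 | 0.27 | 69% | 41% | 79% | 0% |

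The zeros arise because the 90% half-width (for example 1.645 × 0.138 = 0.227) already exceeds 0.20.

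**What a null result leaves open.** With an estimate of exactly zero, the interval still reaches 0.21 to 0.30 SD in favour of the high dose. With an estimate just short of significance in the single-measure cases, it reaches 2 × 0.271 = 0.54 to 2 × 0.295 = 0.59 SD. That is the extreme case, not the typical one.

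**One-sided reading.** If the question is only whether once weekly is no worse (one-sided 0.025, r = .40), power at N = 176 is 82.5% for a 0.40 SD margin and 30% for 0.20 SD. With six-week averaging the latter becomes 31% to 47%.

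**The case against.** The strongest objection is that the article never equates a non-significant result with an inert component or with sameness. A reader might infer that it does, and that the plan automatically picks the shorter package. The text does not support this. Exclusion is provisional and is revisited after interactions are examined. Burden and acceptability are weighed only afterwards, and the preference for the shorter package does not say that sameness is read from a p-value. Mechanism analyses also feed into which components need refinement or reconsideration. For an early-phase screen, keeping components on significance is a defensible selection rule. That part of the objection stands.

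A reader might also infer that a trial of this size cannot show equality at all. That is not so either: equivalence power is 69% to 96% at ±0.40 SD. But this margin is as large as the whole effect the trial is built to find.

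Two further arguments carry some weight. A margin may sit in an analysis plan that is not shown, so its absence from an article is not itself a fault. And the sentence is a discussion remark, next to an admission of limits on dose-finding. Nevertheless, it states positively that the design will yield a clear answer on equal effectiveness, and neither the sizing nor the criterion given in the article provides that. The admitted limit concerns intermediate doses, not what a null comparison means.

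Finally, single-measure figures ignore the six weekly values. This is correct, and the table includes them. They narrow the interval without changing the conclusion.

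**Conclusion.** The point holds for the dose statement in Limitations and for any conclusion that two packages have the same effect. A true 0.20 SD advantage of the high dose would go undetected in about 53% to 74% of trials, and equivalence within ±0.20 SD has at most 18% power. Only a margin near the planning effect of 0.40 SD is reasonably supported.

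These figures assume a two-sided 5% test, 88 analysed per dose level, normal approximations and, for the averaged outcome, an assumed within-person correlation of 0.4 to 0.8. The sample size is not wrong for its stated purpose, and the provisional screening rule is not at fault. What needs correcting is how a null dose result, or apparent sameness, will be interpreted.

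**What to change.** 1. Reword the sentence in Limitations: the trial estimates the dose difference to within about ±0.2 to 0.3 SD, and a non-significant result does not show that the doses are equally effective.
2. Fix a margin in weekly MVPA minutes before analysis. Describe once weekly as being as effective, or two packages as having the same effect, only when the confidence interval for the difference lies inside it. Otherwise report that equality is not established. The margin needs a reason of its own: one equal to 0.40 SD would mean only that the difference is smaller than the effect the trial was powered to find.
3. Keep the provisional include/exclude screen as a selection rule, but report excluded components as not shown to have an effect, rather than as inert.

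The cost is some rewording and one added rule in the analysis plan, with no extra participants. The article says analysis starts only after data collection ends, so the margin can be set without sight of results. The downside is that some comparisons will be reported as inconclusive, and a choice made on burden will then have to be presented as a pragmatic choice.
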